# A novel GnRH antagonist protocol based on LH levels versus traditional flexible GnRH antagonist protocol in PCOS patients undergoing in vitro fertilization: study protocol for a randomized controlled, non-inferiority trial

**DOI:** 10.1186/s13063-022-06586-1

**Published:** 2022-08-13

**Keywords:** IVF, PCOS, LH, Effectiveness, GnRH antagonist protocol

## Abstract

**Background:**

The gonadotropin-releasing hormone (GnRH) antagonist protocol is advantageous given that it can avoid severe ovarian hyperstimulation syndrome (OHSS), especially for patients with polycystic ovary syndrome (PCOS). Basic and clinical evidence has shown that a threshold of luteinizing hormone (LH) stimulation is required for adequate follicular development and oocyte maturation. Ultra-low or high levels of LH are detrimental to pregnancy outcomes. We previously demonstrated that LH could be an indicator for the timing and dosage of antagonist administration in a retrospective study.

**Methods/design:**

In this randomized, single-center, non-inferiority trial, we aim to test the hypothesis that there is no significant difference in cumulative ongoing pregnancy rates between PCOS patients stimulated with LH-based flexible protocol versus traditional flexible GnRH antagonist protocol. The primary efficacy endpoint will be the cumulative ongoing pregnancy rate per cycle. The secondary outcomes will be clinical pregnancy rate, cancelation rate, serious OHSS rate, and cost-efficiency. The cumulative ongoing pregnancy rate per cycle in PCOS women was 80%. Considering that a non-inferiority threshold should retain 80% of the clinical effect of a control treatment, a minimal clinical difference of 16% (two-sided: *α*, 2.5%; *β*, 20%) and a total of 196 patients were needed. Anticipating a 10% dropout rate, the total number of patients required was 216.

**Discussion:**

The results of this study will provide evidence for the efficacy and safety of the LH-based flexible GnRH antagonist protocol in PCOS patients. Moreover, it evaluates the cost-efficiency of both protocols.

**Trial registration:**

Chinese Clinical Trial Registry ChiCTR1800018129. Date assigned: 31 August 2018. Protocol version: 1.0 (18 July 2017)

**Supplementary Information:**

The online version contains supplementary material available at 10.1186/s13063-022-06586-1.

## Background

Polycystic ovary syndrome (PCOS) is the most common heterogeneous endocrine disorder of women and is characterized by a clustering of hyperandrogenism, hypersecretion of luteinizing hormone (LH), and hyperinsulinemia, affecting approximately 9–18% of reproductive-aged women depending on definitions and the populations studied [1, 2]. In these patients, poor quality of oocytes leads to lower fertilization, implantation, and pregnancy rates and a higher miscarriage rate and eventually results in ovarian hyperstimulation syndrome (OHSS) [3–5]. Over the years, gonadotropin-releasing hormone (GnRH) antagonist protocols came to be used more frequently in a wide range of patients, including patients with poor, normal, or high ovarian responses [6, 7]. GnRH antagonist binds competitively to the GnRH receptor of the pituitary gland, but it cannot stimulate the pituitary to release follicle-stimulating hormone (FSH) and LH. According to the timing of initiation for the GnRH antagonist, GnRH antagonist protocols are divided into two types [8]: (i) *fixed protocol*, wherein the GnRH antagonist is initiated at a fixed time, generally in the 5–6 days of ovarian stimulation, and (ii) *flexible protocol*, wherein the antagonist is administered every day when the leading follicles reached 14 mm. It was concluded that a GnRH antagonist protocol is better than a long agonist protocol to reduce the rate of severe OHSS, and there was no difference in ongoing pregnancy, live birth rate, and other indicators between the two protocols [9, 10]. One of the common clinical manifestations of PCOS is the difference in the range of LH production and the variability in the LH:FSH ratio. We first used the LH level as an indicator for the timing and dosage of antagonist supplementation in a previous retrospective study. The results showed that patients with a sustained low LH concentration (LHmax of < 4 IU/L) during ovarian stimulation might not require antagonist administration [11]. In fact, not all PCOS patients had a premature LH surge during ovarian stimulation. On the other hand, part of them will always show a low level of LH. For such patients, the question remains whether it is necessary to add antagonists. For patients with sustained low LH concentration, administration of antagonist, either in traditional fixed or flexible GnRH antagonist protocol, might lead to even lower LH activity. Basic and clinical evidence has indicated that a threshold of LH stimulation is required for adequate follicular development and oocyte maturation. An ultra-low level of LH would do harm to pregnancy outcomes [12]. Our previous retrospective study data indicated that LH-based protocols might improve reproductive outcomes compared with a GnRH agonist during ovarian stimulation in normal responders [11]. A randomized controlled trial conducted in normal responders also showed that the LH-based GnRH antagonist protocol was not inferior to the traditional flexible GnRH antagonist protocol in clinical efficacy, and it was more cost-effective, considering the cumulative ongoing pregnancy rate in the entire assisted reproductive technology (ART) cycle (our unpublished data). However, there are currently limited data for the administration of this protocol in PCOS patients. Therefore, a randomized controlled trial was performed to prospectively compare the efficacy, safety, and cost-effectiveness of the novel LH-based flexible GnRH antagonist protocol with a traditional flexible GnRH antagonist protocol during ovarian stimulation.

## Methods/design

### Study design and recruitment

This is a single-blind, non-inferiority, randomized controlled trial. Patients participating in the trial are undergoing their 1st or 2nd in vitro fertilization (IVF)/intracytoplasmic sperm injection (ICSI) cycle in Beijing Chao-Yang Hospital, Capital Medical University. The research project was approved by the Ethics Committee of Beijing Chao-Yang Hospital and was conducted in accordance with Good Clinical Practices. The study was registered on ClinicalTrials.gov (No: ChiCTR1800018129). Potentially eligible women will be given information about the study at their first consultation. Screening for eligibility will be performed by an authorized investigator on day 2 of the menstrual cycle, after obtaining informed consent from all eligible participants. The study is currently recruiting patients and is expected to be completed by 31 December 2022.

### Eligibility criteria

Women will be enrolled in the study if they fulfilled the following criteria:Inclusion criteria:Infertile women planning a first or second cycle of IVF/ICSI treatmentDiagnosed with PCOS according to the Rotterdam consensus criteria: irregular menstrual cycle, presence of ≥ 12 antral follicles (≤ 9 mm) in each ovary and/or ovarian volume > 10 mL on transvaginal ultrasonographic scanning, and/or clinical/biochemical hyperandrogenism [13]Aged between 20 and 38 years oldExclusion criteria:A partner with azoospermiaRecurrent miscarriage or chromosomal abnormalityUterine fibroids, Mullerian malformations, or adnexal (hydrosalpinx) abnormalitiesClinically significant systemic disease or other endocrine disorders

### Randomization and blinding

Included patients participated in no more than two treatment cycles. Women meeting the inclusion criteria will be randomized according to an online central randomization database (www.medresman.org) in a 1:1 ratio on the day of stimulation. The online sequence is generated and input into the online central randomization system by the staff members who are not involved in enrolling subjects. It is not accessible to any investigators or study coordinators. If a subject fulfills the enrollment criteria, the authorized investigator will log in to the password-protected account to get the assignment. After randomization, patients will be blinded to group allocation and randomly assigned to one of two groups: the control group (traditional flexible GnRH antagonist protocol) or the experimental group (LH-based flexible GnRH antagonist protocol). The nature of the treatment interventions precludes blinding of treating physicians. However, this study will be blinded to embryologists, laboratory technicians, and nurses who conduct follow-ups until the completion of the statistical analysis of this study.

### Sample size calculation

According to the literature and data from our center, the cumulative ongoing pregnancy rate per cycle in women with PCOS in the control arm was around 80%. Considering that a non-inferiority threshold should retain 80% of the clinical effect of a control treatment, a minimum clinical difference of 16% (two-sided: *α*, 2.5%; *β*, 20%) and a total of 196 patients were needed. Considering a possible withdrawal rate of 10%, the total number of patients required will be 216.

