### Statistical analysis

Data analysis of this trial will follow the intention-to-treat principle, including a preliminary comparison of all randomized women in the two groups who did not drop out of the study. Differences between the groups will be compared between demographic variables and baseline information from before the start of the study. Continuous data with normal distribution will be estimated using a two-sample *t*-test, and the Mann-Whitney *U* test will be used for non-normally distributed data. Categorical data will be represented as frequency and percentage, and the differences in these variables will be assessed by the chi-square test or Fisher’s exact test. We will also compute the unadjusted risk ratio (RR) and its 95% confidence interval (CI). This test for non-inferiority will only be performed for the primary outcome; all other secondary outcomes will be tests of superiority. The primary outcome—cumulative ongoing pregnancy rate per cycle in women with PCOS in the control arm—was 80% in our center. Considering that a non-inferiority threshold should retain 80% of the clinical effect of a control treatment, the minimum clinical difference should be 16%. Noninferiority is declared if the upper limit of the two-sided 95% CI for the cumulative ongoing pregnancy rate in the study group does not exceed a relative margin of 16%, equivalent to a two-sided test with an *α* value of 2.5%. A two-sided *α* value of 0.05 is used for superiority testing.

In case of missing values of baseline characteristics, we will analyze them by excluding the missing values, then assign the missing values multiple times, and conduct subsequent analyses to estimate the robustness of the results. For follow-up loss and protocol violation, we will attempt sensitivity analysis to explore the influence of these factors on the trial results.

The flow chart of this study is given in Fig. 1. A schedule of enrollment, interventions, and assessment is provided in the Standard Protocol Items: Recommendations for Interventional Trials (SPIRIT) figure (Fig. 2), and the SPIRIT reporting guidelines are used as shown in Additional file 1 [14].

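### The enrolment total of 216 falls two women short of the 196 the plan needs after its own 10% withdrawal: an arithmetic slip of little consequence for power

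*Protocol article*

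**What the plan says.** The Sample size calculation section builds the trial size in two steps. The first gives the evaluable number: "a minimum clinical difference of 16% (two-sided: *α*, 2.5%; *β*, 20%) and a total of 196 patients were needed". The second adds the allowance for loss: "Considering a possible withdrawal rate of 10%, the total number of patients required will be 216". The abstract (Methods/design) repeats the result: "Anticipating a 10% dropout rate, the total number of patients required was 216". Neither place shows how 196 became 216.

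The Statistical analysis section says the analysis follows intention-to-treat. In the same sentence it describes a preliminary comparison limited to randomized women who stayed in the study. It also plans sensitivity analyses for loss to follow-up. Under Outcome measures, cycles that yield no oocytes or no transferable embryo count as not pregnant, so those women are not lost to the primary outcome.

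**The concern.** A withdrawal rate is a share of the women enrolled. To finish with a given number after 10% withdraw, that number has to be divided by 0.90. Adding 10% of the evaluable number gives a smaller total, and 216 is what that shortcut produces. The recruitment total then does not deliver the evaluable number it was meant to protect, even if every planning assumption holds.

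The numbers 196, 10% and 216 do not fit together, and a reader can see this without knowing the margin, the alpha or the variance formula. What could be at stake is the planned power of the primary non-inferiority comparison, so the size of the gap has to be worked out before it is given any weight.

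**Working it through.** **Inputs**
- Control-arm cumulative ongoing pregnancy rate: about 80% (Sample size calculation).
- Experimental-arm rate: 80%. This is an assumption; the article gives no other expected rate, and its stated aim is to show no significant difference.
- Margin: 16 percentage points, which is 20% of 80% (Sample size calculation).
- Power: 80%, from β of 20% (Sample size calculation).
- Alpha: one-sided 2.5%. The article writes "two-sided: *α*, 2.5%; *β*, 20"%, but its decision rule uses a two-sided 95% confidence interval, which corresponds to one-sided 2.5%.
- Allocation: 1:1 (Randomization and blinding).
- Evaluable target: 196. Withdrawal: 10%. Stated total: 216.

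**Step 1: reproduce 196.** With unpooled variance, n per arm = (z₀.₉₇₅ + z₀.₈₀)² × 2 × 0.8 × 0.2 / 0.16² = 7.849 × 0.32 / 0.0256 = 98.11. That is 196.2 in total, so 98 per arm gives the stated 196. With the same formula, one-sided 1.25% gives 238 and one-sided 5% gives 156. One-sided 2.5% is therefore the level behind the plan's figure. Strict rounding up would give 99 per arm, or 198.

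**Step 2: reproduce 216.** 196 × 1.1 = 215.6, which rounds up to 216 and matches the stated total. That this was the method is an inference from the number.

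**Step 3: test 216 against the target.** 216 × 0.90 = 194.4, so about 194 women (97 per arm) remain. This is two below 196, or one per arm. Put the other way, the 20 added women cover a loss of 20 / 216 = 9.3%, not 10%.

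**Step 4: the consistent total.** 196 / (1 − 0.10) = 217.8, so 218, or 109 per arm. The difference from 216 is two women, 0.9%.

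**Step 5: effect on power.** Power = Φ(0.16 / √(2 × 0.8 × 0.2 / n) − 1.960), with n per arm.

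| Evaluable total | n per arm | Power |
|---|---|---|
| 194 | 97 | 79.55% |
| 196 | 98 | 79.96% |
| 198 | 99 | 80.35% |

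The allowance costs 79.96 − 79.55 = 0.41 percentage points. Enrolling 218 leaves 218 × 0.90 = 196.2 women, which restores 79.96%.

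**The case against.** The strongest reply is that nothing turns on two women. The control rate is given only as around 80% and the withdrawal rate only as possible. A true rate of 80.3% in both arms would make 97 per arm enough for 80% power: 7.849 × 2 × 0.803 × 0.197 / 0.0256 = 97.0. The gap is smaller than the precision of the inputs. This stands, and it settles how much weight the point can carry. It does not make 216 consistent with 196 and 10%.

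A second reply concerns the analysis set. If every randomized woman is analysed, as the intention-to-treat statement suggests, all 216 count and there is no shortfall. This stands in part. The Statistical analysis section says both things, so the shortfall applies to the comparison of women who stayed in the study. It would go too far to say that this is the only comparison planned. However, adding an allowance for withdrawal at all presupposes that withdrawn women do not contribute to the 196.

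Third, a reader might infer that the allowance is what takes the trial below 80% power. The figures do not support that. At 196 the power is already 79.96%, before any withdrawal, and 218 only brings it back to that value. Anyone who insists on 80% to the decimal would need 198 evaluable and 198 / 0.90 = 220 enrolled. Anyone who accepts 79.96% as 80% can accept 79.6% as well.

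Fourth, a reader might link this point to the wording of alpha as two-sided 2.5% and infer a larger loss of power. That is a separate question about how the significance level is written. It would affect 196 just as much as 194, and it owes nothing to the withdrawal allowance.

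**Conclusion.** The point holds as a minor arithmetic correction. By the plan's own inputs, 216 women less 10% leaves about 194, two short of the 196 it says are needed; the matching total is 218. The conclusion that 216 does not preserve 196 rests only on the three stated numbers and on withdrawn women leaving the analysis. The power figures also assume 80% in both arms, a 16-point absolute margin, one-sided 2.5% and an unpooled normal approximation. On those assumptions the cost is about 0.4 percentage points, 79.6% against 79.96%. It is not a real power deficit and gives no reason to doubt the design. That the total came from multiplying by 1.1 fits the number exactly, but the article does not say so.

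**What to change.** Make one of two changes, in both the abstract and the Sample size calculation section:

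- Keep 216, and state that after 10% withdrawal it leaves about 194 evaluable women and about 79.6% power under the planning assumptions.
- Correct the total to 218 (109 per arm) and show the step 196 / (1 − 0.10) = 217.8.

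The first costs one sentence and no recruitment. The second costs two more women; Trial status reports more than 180 enrolled with enrolment still open at submission, so this was feasible then. In either case, the same sentence should say whether withdrawn women are left out of the primary comparison, since the allowance depends on it.

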### Interventions

#### Adherence

Participants are fully informed that the trial does not involve the increase of drug types, blood test, and patient visits, which is easy for them to accept. The duration of ovarian stimulation ranges between 8 and 11 days for most patients. It will be finished by one fixed clinician for each participant. The attending in charge system will improve the relationship between clinicians and participants. They can consult the clinician in the clinic at each visit about the treatment regimen and adverse effects if any. Besides, psychological phenomena (e.g., depression and anxiety) can be reduced to improve adherence.

#### Ovarian stimulation

The ovarian stimulation is initiated from days 2 to 3 of the menstrual cycle. Baseline pelvic ultrasound and serum E_2_, FSH, LH, progesterone (P), and beta-human chorionic gonadotropin (β-hCG) were measured. Recombinant FSH (rFSH; Gonal-f, Merck, Germany) at a dose of 150–300 IU/day is administered depending on patient age, body mass index (BMI), anti-Mullerian hormone (AMH), antral follicle count (AFC), and basal serum FSH concentration. Five days later, the doses are adjusted according to ultrasound examination, follicle development, and serum hormone levels.

For the traditional flexible GnRH antagonist protocol, GnRH antagonist (Cetrotide, 0.25 mg per day; Merck, Germany) is initiated and continued up until and including the day of trigger, once the E_2_ concentration is ≥ 300 pg/mL or the leading follicle reaches a size of 14 mm.

For the LH-based flexible GnRH antagonist protocol, the timing and dosage of antagonist administration are based on the serum LH levels from day 5 of ovarian stimulation. The blood test will be performed 3–4 times until trigger. No antagonist is administered if the LH level was ≤ 4 IU/L. 0.125 mg of cetrorelix acetate is administered daily if the LH concentration is > 4 IU/L and ≤ 6 IU/L, until the next blood test. 0.25 mg of cetrorelix acetate is administered daily if the LH concentration was > 6 IU/L and ≤ 10 IU/L, until the next blood test. If the LH concentration is > 10 IU/L and ≤ 15 IU/L, 0.375 mg of cetrorelix acetate is administered daily for 1 day. If the LH concentration is > 15 IU/L, 0.5 mg of cetrorelix acetate is administered for 1 day. The need for antagonist co-treatment is dependent on an LH concentration of > 4 IU/L until the day of trigger. After two or more follicles reach a diameter ≥ 18 mm, 0.2 mg triptorelin and 2000–3000 IU of hCG will be injected. Serum LH, E_2_, and P concentrations are measured.

#### Oocyte retrieval, in vitro fertilization, and embryo transfer

Transvaginal ultrasound-guided oocyte retrieval will be performed 36 h later. Retrieved oocytes are fertilized by either IVF or ICSI, depending on sperm quality. For participants receiving fresh embryo transfer (ET), transfer is performed with two of the highest quality embryos at the cleavage stage 3 days after oocyte retrieval. Luteal-phase support with vaginal progesterone gel (Crinone, Merck Serono) at a dose of 90 mg daily and oral dydrogesterone (Duphaston, Abbott) at a dose of 10 mg twice daily is started after oocyte retrieval and continued until the day of hCG testing. If pregnancy is achieved, luteal phase support will be continued until 10 weeks’ gestation. Frozen ET will be taken if patients are at risk of OHSS; have an unfavorable endometrium (endometrial thickness of ≤ 6 mm or ≥ 16 mm, cavity fluid, or endometrial polyps); or have a P concentration of ≥ 1.5 ng/mL on the day of hCG trigger. For frozen ET, the endometrium is prepared using either a natural cycle regimen or an artificial cycle regimen based on the physician’s decision. For the natural cycle regimen, luteal phase support is started from the ovulation day with oral dydrogesterone (10 mg twice daily). For the artificial cycle regimen, the endometrium is prepared with oral estradiol valerate at a dose of 6–8 mg daily which will be started on days 3–5 of the menstrual cycle. Vaginal progesterone gel (90 mg daily) and oral dydrogesterone (10 mg twice daily) are added when the endometrium thickness reaches 8 mm. If pregnancy is achieved, luteal phase support will be continued until 10 weeks’ gestation.

Concomitant treatments such as traditional Chinese medicine and acupuncture are not permitted during the trial.

### Outcome measures

The primary outcome will be the cumulative ongoing pregnancy rate resulting from one ART aspiration cycle, including fresh and FET cycles. Ongoing pregnancy is defined by the presence of a gestational sac with a fetal heartbeat after 12 weeks of gestation. The cycle in which no oocytes are retrieved or no embryo is available for transfer will be considered as not getting pregnant. Secondary outcomes will be high-quality embryo rate, clinical pregnancy rate, severe OHSS rate, and cancelation rate. Moreover, differences in cost-effectiveness and adverse events will be evaluated. Typically, a high-quality embryo is defined as an embryo with 7–10 cells and ≤ 25% fragmentation developed from 2PN embryos on day 3 after oocyte aspiration. The clinical pregnancy rate is defined as the presence of a gestational sac at 6–7 weeks of gestation when visualized by transvaginal ultrasound. Moderate OHSS is diagnosed when ovarian enlargement of > 5 cm and < 12 cm is observed and when ultrasonographic ascites are present with or without nausea, vomiting, and/or diarrhea. Severe OHSS is diagnosed when ovarian enlargement of ≥ 12 cm is observed and when there is clinical evidence of ascites and/or hydrothorax or breathing difficulties with or without hemoconcentration, severe hypoproteinemia, abnormal liver function, coagulation abnormalities, or diminished renal function.

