### Data monitoring and safety

All data will be supervised by independent statisticians from Beijing Chao-Yang Hospital. All clinical research will be carried out as per the Good Clinical Practice (GCP) standards. The study site monitor will check the maintenance of trial-related source records, authenticity, and integrity of the data regularly to ensure adherence to the protocol, standard operating procedures, and applicable regulatory requirements. Adverse events (AEs) are defined as any undesirable event experienced by a subject during a clinical trial, regardless of whether the event is considered related to the intervention. Routine assessments for OHSS were performed on day 2 after oocyte retrieval in both groups. At all other times, OHSS will be evaluated and classified if symptoms are reported by the patient. A serious adverse event (SAE) is defined as any untoward medical occurrence or effect that results in death, is life-threatening (at the time of the event), requires hospitalization, prolongs an existing hospitalization, results in persistent or significant disability or incapacity, is a congenital anomaly or birth defect, and is a new event of the trial likely to affect the safety of the subjects such as an unexpected outcome of an adverse reaction. All AEs reported spontaneously by the subject or observed by the investigator or their staff will be recorded accurately in the eCRFs and will be followed up during the course of the AE until their resolution or for 2 weeks after the end of the trial. All SAEs will be reported to the investigators, discussed through a web-based AE reporting system, and will be reported to the Pharmaceuticals and Medical Devices Agency, if necessary. There will be an interim analysis. If the data show convincing evidence of harm, such as a high cancelation rate due to premature LH surge, the trial would be stopped by the investigators or the data monitoring committee.

Over the course of the trial, some tiny modifications, such as modification of the follow-up method from telephone to short message for some subjects, will not trigger a protocol amendment. However, protocol amendment will be performed if the most relevant and critical modifications that affect the trial design and data collection procedure occurred. A modified version, if applicable, will be submitted to the sponsor for funding, to the IRB for ethics approval, and to the data monitoring committee.

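### The primary outcome has no single unit: it is tied to an aspiration cycle in one place and given per cycle elsewhere, so cycles cancelled before retrieval can be either counted as failures or left out

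*Protocol article*

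**What the plan says.** All places are in the protocol article.

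- **Randomization and blinding:** women are allocated "in a 1:1 ratio on the day of stimulation", so before any retrieval.
- **Outcome measures, unit:** "The primary outcome will be the cumulative ongoing pregnancy rate resulting from one ART aspiration cycle, including fresh and FET cycles".
- **Outcome measures, failure rule:** "The cycle in which no oocytes are retrieved or no embryo is available for transfer will be considered as not getting pregnant". Cancelation is not named in this rule. It appears in the next sentence as a secondary outcome: "Secondary outcomes will be high-quality embryo rate, clinical pregnancy rate, severe OHSS rate, and cancelation rate".
- **Abstract, Methods/design:** "The primary efficacy endpoint will be the cumulative ongoing pregnancy rate per cycle". Sample size calculation and Statistical analysis also give the 80% control rate per cycle.
- **Statistical analysis, population:** intention-to-treat, described as "including a preliminary comparison of all randomized women in the two groups who did not drop out of the study". Dropout is not defined.
- **Data monitoring and safety:** the example of harm that could stop the trial is "such as a high cancelation rate due to premature LH surge".

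**The concern.** A woman whose cycle is cancelled during stimulation has been randomised but has no aspiration. If the unit is the cycle started, she is in the denominator as a failure. If the unit is the aspiration cycle, she can be treated as having no cycle to evaluate. The two units differ by exactly the women cancelled between randomisation and retrieval.

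That group matters here because the strategies differ in when and how much antagonist is given. The protocol itself names cancelation after a premature LH surge as the harm to watch for. If such cancelations were more frequent in the LH-based arm and were left out, the comparison would lose failures mainly from that arm, and in a non-inferiority trial this error is anti-conservative. Treating physicians know the allocation, so the choice of reading should not be left until after the data are in.

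**Working it through.** **1. Planned size.** Inputs from Sample size calculation: 80% in both arms, difference of 16 points, 80% power. The stated 2.5% is taken as one-sided, which matches the two-sided 95% interval in Statistical analysis.

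n per arm = (1.960 + 0.842)² × 2 × 0.80 × 0.20 / 0.16² = 98.1, which rounds up to 99 (198 in total). The article states 196, or 98 per arm, where power is 0.80. The figure reproduces, so 98 per arm is used below.

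**2. Assumptions for the illustration.** The documents give no cancelation rate. The following are assumed:
- cancelation before aspiration of c₀ = 2% in control and c₁ = 5%, 10% or 15% in the LH-based arm
- 80% ongoing pregnancy among aspirated women in both arms
- an absolute margin of 16 points, tested with the two-sided 95% interval for the difference in rates

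**3. Formulas.** Rate per randomised woman = 0.80 × (1 − c). Number aspirated = 98 × (1 − c).
P(non-inferiority) = Φ[(0.16 − (p_C − p_T))/SE − 1.96], with SE = √[p_C(1 − p_C)/n_C + p_T(1 − p_T)/n_T].

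**4. Worked case, 2% v 10%.**
- Per woman: rates 0.784 and 0.720, deficit 0.064, SE = √(0.784 × 0.216/98 + 0.720 × 0.280/98) = 0.0615. Then (0.16 − 0.064)/0.0615 − 1.96 = −0.40, probability 0.34.
- Per aspiration: 0.80 in both arms, n = 96.04 and 88.2, SE = 0.0590. Then 0.16/0.0590 − 1.96 = 0.75, probability 0.77.

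**5. Results.**

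| Cancelation, control v LH-based | True deficit per woman | Non-inferiority declared, per aspiration | Non-inferiority declared, per woman |
|---|---|---|---|
| 2% v 2% | 0 | 79% | 78% |
| 2% v 5% | 2.4 points | 79% | 62% |
| 2% v 10% | 6.4 points | 77% | 34% |
| 2% v 15% | 10.4 points | 76% | 14% |
| 5% v 2% | −2.4 points | 79% | 87% |

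With equal cancelation the expected difference is zero on either denominator. If cancelation is higher in control, the per-aspiration denominator works against the LH-based arm.

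**6. False non-inferiority at the margin.** Set the true per-woman rates at 80% v 64%, a 16-point deficit. Per woman, non-inferiority is declared in 2.5% of trials. Per aspiration, the control rate is 0.80/0.98 = 81.6%. The LH-based rate is 0.64/0.95 = 67.4%, 0.64/0.90 = 71.1% or 0.64/0.85 = 75.3%. The apparent deficits are 14.3, 10.5 and 6.3 points, and false non-inferiority is about 4.6%, 14% and 35%.

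**The case against.** The strongest objection is that the text already counts cancelled cycles as failures. A cycle stopped during stimulation is literally one with no oocytes retrieved and no embryo for transfer, so it meets both limbs of the failure rule. The subject of that rule is the cycle, not the aspiration. The aspiration-cycle phrase may only bound which fresh and frozen transfers are accumulated. The analysis starts from all randomised women, and nothing equates a medically cancelled cycle with dropout.

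This has force. A reader might infer that the plan removes these women from the denominator and so biases the trial towards non-inferiority. The documents do not support that: no sentence excludes them, and the literal failure rule points towards counting them.

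The ambiguity nevertheless remains. The failure rule follows an outcome defined by an aspiration cycle, so it can also be read as covering only an aspiration that yields nothing. The intention-to-treat sentence removes women who dropped out without saying whether a cancelled cycle is a dropout.

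The direction of any bias is also open. The LH-based arm gives no antagonist or a lower dose at low LH, but at high LH more than the control arm's daily dose. Higher cancelation in that arm is therefore a possibility that the protocol guards against, not a stated expectation. Cancelation is also compared as a secondary outcome, and harm of this kind can stop the trial, so a large imbalance would be visible. Visibility does not settle how these women enter the primary analysis.

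Finally, a condensed article may leave a full list of failed-cycle types to other documents. Here, however, the article itself states the unit and a failure rule, and its sections do not agree on the unit.

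**Conclusion.** The point holds as an inconsistency in the unit of the primary outcome. One reading keeps women cancelled before retrieval as failures and another leaves them out, and the article does not exclude the second. It would be too strong to say that these women are excluded, or that the trial is biased as written.

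The size depends on unequal cancelation, for which the documents give no figure. Under the stated assumptions, a move from 2% v 5% to 2% v 15% lowers the chance of declaring non-inferiority per randomised woman from 62% to 14%, while per aspiration it stays at 76% to 79%. With equal cancelation the choice causes no bias in the expected difference. Because the ambiguity sits in the primary outcome and could decide the conclusion, it should be closed before analysis. Enrolment was still under way when the article was submitted.

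**What to change.** - **Outcome measures:** define the primary outcome per randomised woman, as an ongoing pregnancy from the fresh or frozen transfers of the stimulation cycle started at randomisation. State that a cycle cancelled before aspiration for any reason, like one with no oocytes or no embryo, counts as not pregnant.
- **Statistical analysis:** state that a cancelled cycle is not a dropout.
- **Abstract, Sample size calculation and Statistical analysis:** use the same denominator, and say whether the 80% control rate was per started cycle or per aspiration.
- **Secondary description:** report the per-aspiration rate only in this role.

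The cost is wording. Cancelation is already an outcome, so no new data are needed. The observed rates will be slightly lower. If the 80% was per aspiration, 2% cancelation makes it 0.80 × 0.98 = 78.4% per woman. With 98 per arm, SE = √(2 × 0.784 × 0.216/98) = 0.0588, and power is Φ(0.16/0.0588 − 1.96) = about 78% instead of 80%.
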